### Cardiopulmonary bypass

CPB will be performed in mild to moderate hypothermia on a conventional CPB circuit with cardiac arrest induced by antegrade or retrograde infusion of cold crystalloid cardioplegic solution. Extracorporeal circulation will be performed with a pump flow of 2.2–2.5 L min^−1^ m^−2^. Prior to CPB, 300–350 IU kg^−1^ heparin will be administered to achieve an activated clotting time of > 400 s. After weaning from CPB, heparin will be antagonized with protamine in a ratio of 1:1. Furthermore, propofol TCI will be stopped and the investigational treatment will be re-administered.

### Intensive care unit treatment

On the ICU, analgesia will be achieved with a continuous infusion of piritramide, supplemented by systemic acetaminophen (1–2 g, administered IV every 8 hours) during the first postoperative day. Standard tracheal extubation and patients discharge criteria will be applied.

As part of standard care, a bundle of non-pharmacological interventions will be applied to prevent delirium, including:Active detection and treatment of painEarly mobilizationRemoval of catheters, drains, probes, etc. as soon as possibleTimely recognition and treatment of medical problems such as stroke, infections, electrolyte imbalances, hypoxia, heart failure, hypotension, dehydration, urinary retention, etc.Strict avoidance of medications known to trigger POD (in particular, benzodiazepines and steroids)

Whenever a POD occurs, pharmacological treatment based on our institutional standards of care, will be intiated.

Once standard discharge criteria will be met, the patients will be transferred to the ward.

### Study outcomes

#### Primary endpoint

Incidence of postoperative delirium as assessed by 3D-CAM and/or CAM-ICU.

The primary study endpoint will be the incidence of POD during the first 5 postoperative days. Hence, the null hypothesis states that there is no difference between both groups in POD incidence (yes/no) during the first 5 postoperative days. Through ICU-stay, patients will be assessed daily for the presence of POD by trained research nurses (blinded to the group assignment) using the CAM adapted for the ICU (CAM-ICU) [34]. In addition, we will perform a daily chart review for the results of the Intensive Care Delirium Screening Checklist (ICDSC) [35] over the previous 24 hours, which is a standard assessment, conducted during each 8-hour shift by the bedside ICU nurse. Patients with a Richmond Agitation-Sedation Scale of < −3 will be considered unconscious and not evaluable for POD [36]. After transferal to the ward, patients will be assessed by trained research personnel on a daily basis for the presence of POD using the 3D-CAM. In addition, we will perform a daily chart review for the results of the Delirium Observation Scale (DOS) [37] over the previous 24 hours that will be conducted by the nurses. On both the ICU and the ward, the patients’ records over the previous 24-hour period will be checked to identify key words suggestive of POD (e.g. confused, agitated, aggressive, disorientated, drowsiness and delirious) and the administration of antipsychotic therapy [38, 39].

#### Secondary endpoints

Secondary endpoints include the duration of POD (total number of days and percentage of patients with duration of POD longer than 2 days; for patients who have POD on day 5, daily clinical assessments are continued until the symptoms resolve or until the patient is discharged), the severity of POD (assessed with the delirium severity measure based on CAM (CAM-S) [40], use of physical restraints, postoperative cognitive function as analyzed with the MMSE at postoperative day 3, day 5, the day before discharge and at 6 months post surgery, and preoperative and postoperative ADL functioning as analyzed with the Katz ADL scale at baseline and the day before discharge and at 6 months post surgery.

In addition, the administration of anti-delirium medications (such as haloperidol, anxiolytics, dexmedetomidine, etc.) and duration of sedation will be registered and compared between both groups.

Other secondary endpoints will be:Incidence of MACCE (major adverse cardiac and cerebral events, occurring until discharge from hospital and in the first 6 postoperative months); i.e. death from any cause; perioperative myocardial infarction, requirement of surgical revisions at the coronary arteries; postoperative coronary angioplasty; and stroke. Myocardial infarction is defined as the occurrence of a new Q wave in addition to a rise of more than 10 ng ml^−1^ of troponin in the early postoperative period or any episode of chest pain with typical rise and fall of cardiac enzymes thereafterOther cerebrovascular accidents not included in MACCE (transient ischemic attacks, reversible ischemic neurologic deficit)Postoperative renal function (as assessed by serum creatinine and blood urea nitrogen (BUN) levels)Requirement for blood (product) transfusionIncidence of intraoperative awareness as detected by the use of a structured Brice questionnaire [41] that will be performed one day after ICU dischargeDuration of postoperative ICU-stay and hospital staySeverity of postoperative critical illness as indicated by the Acute Physiology and Chronic Health Evaluation (APACHE) [42] II score once within 24 hours after admission to the ICU and the Sequential Organ Failure Assessment (SOFA) score [43]Incidence of serious adverse events (SAE) and suspected unexpected serious adverse reactions not included above. According to the International Conference on Harmonization of Technical Requirements for Registration of Pharmaceuticals for Human Use (ICH), an adverse event (AE) will be defined as “any untoward medical occurrence in a patient or clinical investigation subject administered a pharmaceutical product and which does not necessarily have to have a causal relationship with this treatment.” A SAE is “any AE that is life threatening – results in death – requires patients re-hospitalization and/or prolongation of existing hospitalization – or results in patient’s disability” [44]Intraoperative hemodynamic and respiratory profileIntraoperative use of inotropic/vasoactive medication

### Blood samples and laboratory parameters

Because of a possible correlation between preoperative vitamin D levels and the occurrence of POD, serum-levels of 25-hydroxy vitamin D (25-OHD) will be checked for all patients preoperatively [45, 46]. Furthermore, different blood samples will be collected at baseline (visit 0), at 1 hour after end of surgery (visit 2) and postoperative day 1 (visit 3). From these samples, the following parameters will be examined:Markers of glial injury: serum protein S100βHemoglobin and hematocritCardiac markers: CK-MB and troponin T-hsC-reactive protein (CRP), leukocyte counts, serum cytokines (interleukin (IL)-6, IL-10)Respiratory markers: SaO_2_, PaO_2_ PaCO_2_, arterial pH, bicarbonate and base excessRenal markers: serum creatinine and blood urea nitrogenHepatic markers: serum alanine aminotransferase (ALT), aspartate aminotransferase (AST), gamma-glutamyl transferase (GGT) and total bilirubinSerum electrolytes and serum blood sugar concentration

Additional blood samples may be collected, at the investigator’s or other physician’s judgment, in case of technical problems during the initial assay performed or missing baseline values prior to surgery and/or clinical abnormalities necessitating specific additional measurements.

### Statistical analysis and sample size calculation

All statistical analyses will be performed using a commercially available software package (SAS software, version 9.2 of the SAS System for Windows, SAS Institute Inc., Cary, NC, USA). All tests will be 2-sided, and a *p* < 0.05 will be considered to indicate statistical significance.

For the primary outcome, the incidence of POD, a logistic regression adjusting for the stratification variable EuroSCORE will be used to compare both groups. Sensitivity analyses will be performed to evaluate the impact of the non-evaluable patients (expected to be less than 5 %: e.g. deceased patients, transferred to other centers, extremely sedated patients) during the 5 postoperative days. First, a “worst case scenario” will be considered assuming absence of POD for all non-evaluable patients in the conventional anesthesia group and presence of POD for all non-evaluable patients in the xenon-anesthesia group. Second, a multiple imputation approach will be used imputing a POD value for the non-evaluable patients, with as imputation model a logistic regression fitted in both groups separately [47] with baseline characteristics as categorical and continuous predictors. Twenty imputed datasets will be created and results will be averaged appropriately.

For the secondary outcomes, the used statistical test will depend on the type and distribution of the considered outcome. Normally distributed data (verified with the Shapiro-Wilk *W* test statistic) will be compared using an analysis of covariance (ANCOVA) with the dichotomized EuroSCORE as binary covariate. Intergroup comparisons of non-normally distributed data will be performed using the stratified version of the Mann–Whitney *U* test. Differences in proportions will be analyzed using the exact test for a stratified 2x2 table. Time-to-events (occurrence of POD) will be assessed from end of surgery until the occurrence of the POD. Patients will be censored if they do not experience POD at the time of the last follow-up. To obtain the cumulative distribution curves for the POD times, Kaplan-Meier estimates will be used and groups will be compared using the stratified log-rank test. A linear model for longitudinal measurements with an unstructured covariance matrix for the fixed points in time (i.e. a multivariate regression model using a direct likelihood approach) [48] and the dichotomized EuroSCORE as a binary covariate will be used to evaluate the evolution of laboratory markers.

The study will be powered to detect the differences in primary outcome between the sevoflurane-group and the xenon-group. Based on recent observations from our institute [49], the incidence of POD after cardiac surgery with sevoflurane-anesthesia is approximately 40 %. A comparable incidence has already been reported earlier by our group [50] and has also been observed by other investigators [3]. Using a 2-sided test for the detection of differences between proportions (with alpha = 5 % and applying a continuity correction), at least 91 patients per group (182 in total) are required to show with 80 % power a 50 % reduction in the incidence of POD. To compensate for possible drop-outs, we will include 190 patients in total. They will be randomized into both groups in a 1:1 ratio.

Since the needed sample size depends extremely on the assumed POD rate, a sample size recalculation (SSR) will be performed after inclusion of 100 patients. This SSR will be based on a blinded evaluation of the overall POD rate [51]. Since the SSR is fully blinded (i.e. the group allocation is not known), this analysis can be performed by a member of the study steering committee. Applying the assumed relative risk (relative reduction of the POD by 50 %) on the overall POD rate, the power will be recalculated. For example, suppose that the overall POD rate after inclusion of 50 subjects in each group equals 24 %, instead of the expected 30 % (40 % and 20 %, respectively). Then, based on the assumed 50 % relative reduction, this corresponds to 16 % and 32 % for xenon and sevoflurane, respectively, which would require 123 patients in each group instead of 91 patients to maintain 80 % power. Based on this information, the study steering committee will decide on extending the accrual time. Note that based on the result of the SSR, the planned sample size will only be maintained or increased (not lowered).

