## Background

Postoperative delirium (POD) is frequently observed after cardiac surgery with incidences ranging from 20 to 80 % [1, 2]. It is associated with short-term complications such as an increase in mortality, morbidity, costs and length of stay, but is also associated with long-term sequelae, including the development of persistent cognitive deficits, loss of independence, and increased mortality for up to 2 years [3].

The pathophysiology of POD is complex and thought to be related to cerebral ischemia-reperfusion injury, endothelial dysfunction [4], neuroinflammation [5], neurotransmitterimbalances [6, 7] and direct neurotoxic effects of anesthetics [8]. The individual baseline risk of a patient to develop POD is determined by a variety of predisposing factors that are not possible to be modified, including age, male gender, psychiatric illness, cognitive impairment (e.g. dementia) and atherosclerotic disease [2].

POD has been suggested to be precipitated by intraoperative and postoperative triggers. In contrast to the predisposing factors, precipitating factors are amenable to modification and have thus become a target of prevention strategies. Unfortunately, the unambiguous identification of precipitating factors for POD remains notoriously difficult. Numerous elements have been described, including (but not limited to) cardiovascular surgery, use of cardiopulmonary bypass (CPB), application of anesthetics and cognitively active medication, hypotension, decreased cardiac output, hypothermia and hypoxia [9, 10].

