### Randomization

Patients will be randomized using a computer-generated permuted block randomization sequence (variable block-size, 1:1 allocation). Randomization will be stratified by the European System for Cardiac Operative Risk Evaluation (EuroSCORE) II (Stratum I: EuroSCORE ≤ 3; Stratum II: EuroSCORE > 3). A masked randomization procedure will be used in which group assignments are hidden in sealed, opaque, sequentially numbered envelopes that will only be opened upon arrival of the patient to the operation room (OR).

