#### Baseline assessment (Investigator I)

Investigator I will obtain written informed consent and record baseline data (demographic data, medical and surgical history, routine clinical examination, Charlson comorbidity index (CCI) [28], results of preoperative chest X-ray, electrocardiogram (ECG) analysis, echocardiography and standard laboratory parameters). In addition, the MMSE [29], the 3D-CAM, the Geriatric Depression Scale (GDS) [30] and an interview with a family member using the short form of the Informant Questionnaire on Cognitive Decline in the Elderly (IQCODE) [31] will be performed the day before surgery. Patients with alcohol abuse will be identified with the CAGE questionnaire [27] and excluded. Besides, patients’ preoperative functional status will be assessed using the Katz Index of Activities of Daily Living (ADL) [32].

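### The primary model adjusts only for the binary EuroSCORE stratum; prespecifying age and baseline MMSE as well would probably add a few points of power to an already valid analysis

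*Protocol article*

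**What the plan says.** The section on statistical analysis and sample size fixes the primary comparison: "a logistic regression adjusting for the stratification variable EuroSCORE will be used to compare both groups". Under Randomization the variable has two levels: "Stratum I: EuroSCORE ≤ 3; Stratum II: EuroSCORE > 3". The same section refers to the dichotomised score when it describes the secondary analyses, so the binary reading is the natural one. No other covariate is named for the primary model.

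The Background says that a patient's baseline risk of postoperative delirium (POD) depends on "predisposing factors that are not possible to be modified, including age, male gender, psychiatric illness, cognitive impairment (e.g. dementia) and atherosclerotic disease". The baseline assessment, done before surgery, covers "demographic data, medical and surgical history, routine clinical examination" and continues: "In addition, the MMSE [29], the 3D-CAM, the Geriatric Depression Scale (GDS) [30] and an interview with a family member". Age and a cognitive score are therefore scheduled pre-treatment measurements.

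Baseline characteristics do appear as predictors in the statistical section, but only in the multiple-imputation model for non-evaluable patients, who are expected to be fewer than 5 %.

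The sample size is an unadjusted comparison of two proportions with continuity correction, sized "to show with 80 % power a 50 % reduction in the incidence of POD". It claims no gain from covariates.

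**The concern.** The protocol treats age and cognition as determinants of the outcome, collects them, and uses baseline data to impute that outcome, yet the comparison that decides the trial leaves them out. With one binary endpoint and 190 patients, adjustment for prognostic baseline covariates is one of the few ways to gain power without more patients. It would also correct the estimate for chance imbalance in age or cognition that the EuroSCORE stratum does not capture. The choice has to be made before unblinding, because a covariate chosen afterwards is open to the charge of being data-driven.

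**Working it through.** **1. The plan's own figures.** Inputs from the sample size section: 40 % versus 20 %, two-sided 5 %, 80 % power, continuity correction.

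- Uncorrected n = [1.96·√(2·0.3·0.7) + 0.8416·√(0.4·0.6 + 0.2·0.8)]² / 0.2² = (1.2702 + 0.5323)² / 0.04 = 81.2, so 82 per group.
- Corrected n = (81.2/4)·[1 + √(1 + 4/(81.2·0.2))]² = 90.9, so 91 per group, as stated.
- The same formulas at 32 % versus 16 % give 111 uncorrected and 123 corrected. The recalculation example (123) is reproduced too.

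**2. Power of the planned analysis.** A logistic Wald test carries no continuity correction. At 91 per group, z = (0.2·√91 − 1.2702)/0.6325 = 1.008, so power is 84.3 %. The 80 % target is met with some room.

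**3. Gain from two covariates.** The documents give no prognostic strength, so it was assumed and varied. The simulation used 6000 trials per row, 91 per group, marginal rates held at 40 % and 20 %, a balanced binary stratum (assumed odds ratio 1.5), and two independent standard-normal covariates standing for age and MMSE. Both models were fitted to the same simulated trials.

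| Assumed OR per SD, each covariate | AUC of the two | Power, stratum only | Power, plus two covariates | Mean OR for arm, stratum only → adjusted |
|---|---|---|---|---|
| 1.0 | 0.50 | 84.6 % | 84.7 % | 0.365 → 0.360 |
| 1.3 | 0.60 | 84.9 % | 85.9 % | 0.361 → 0.347 |
| 1.5 | 0.65 | 84.6 % | 86.4 % | 0.362 → 0.334 |
| 1.8 | 0.71 | 84.9 % | 88.0 % | 0.362 → 0.313 |
| 2.0 | 0.74 | 84.1 % | 89.1 % | 0.367 → 0.300 |
| 2.5 | 0.79 | 84.4 % | 91.7 % | 0.364 → 0.265 |

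The simulation error of one power figure is about √(0.85·0.15/6000) = 0.5 points. A second set-up, with a single prognostic index correlated 0.4 with the EuroSCORE stratum and 3000 trials per scenario, gave similar gains: 84 to 86 % at AUC 0.63, 84 to 87 % at 0.70, 85 to 90 % at 0.74 and 85 to 92 % at 0.79.

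**4. Type I error.** With 30 % in both groups and odds ratios per SD of 1.5 and 2.0, it was 4.5 to 4.7 % for the planned model and 4.8 to 4.9 % for the adjusted one.

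**5. A lower event rate.** At the protocol's own 32 % versus 16 % with 91 per group, power goes from 73.2 to 74.9 % (OR 1.5 per SD) or from 72.0 to 77.9 % (OR 2.0 per SD).

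**6. Can the model be fitted?** Expected events are 91·0.40 + 91·0.20 = 54.6, about 55. Four terms (arm, stratum, age, MMSE) leave about 14 events per term.

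**7. Effect measure.** At the design rates the risk ratio is 0.20/0.40 = 0.50, the risk difference is −0.20, and the marginal odds ratio is (0.20/0.80)/(0.40/0.60) = 0.375. The last column of the table shows the odds ratio moving further from 1 as covariates are added although the marginal risks are unchanged: a covariate-conditional odds ratio is a different quantity.

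**The case against.** The strongest reply is that nothing here is wrong. The model adjusts for the variable used to stratify randomisation, keeps its type I error and exceeds the promised power at the design rates. If the event rate is lower, the blinded recalculation can raise the sample size. Extra covariates could also be added in an analysis plan that is not shown. All of this stands, and it limits the point to a recommendation. What remains is that the article does fix the primary model, with one covariate.

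The reply is also right that the gain may be small. Eligibility is limited to patients over 65, and dementia, which the Background gives as its example of cognitive impairment, is excluded. Both narrow the range of the covariates. The Background does not name the MMSE score itself as a risk factor, and nothing shows that it is strongly prognostic in patients without dementia.

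Three stronger readings are tempting but unsupported:

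- **Power is given up at no cost.** Adjustment makes the odds ratio conditional, and the MMSE is scheduled but not guaranteed for every patient, so missing values need a rule.
- **The odds ratio contradicts the hypothesis.** The null hypothesis is no difference in incidence, and an odds ratio of 1 is the same null as a risk ratio of 1. The 50 % reduction is a planning assumption, and the article does not say which effect measure will be the headline. The issue concerns reporting only.
- **Chance imbalance undermines the test.** With 91 per group, a standardised covariate differs between arms with SD √(2/91) = 0.15, so about one trial in 20 exceeds 1.96·0.148 = 0.29 SD. The unadjusted test keeps its size on average regardless; adjustment sharpens the estimate.

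**Conclusion.** The point holds as a missed efficiency gain. The planned primary analysis is valid and has about 84 to 85 % power at 91 per group for 40 % versus 20 %. Adding age and baseline cognition would gain roughly 1 to 2 points at an odds ratio of 1.3 to 1.5 per SD for each, 3 to 5 points at 1.8 to 2.0, and nothing if neither predicts delirium. The 7-point gain at 2.5 needs stronger predictors than the documents give reason to expect, and the restricted age and cognition ranges point to the lower end. The result rests on assumed prognostic strengths and on covariates that are normal and linear on the logit scale. Power did not fall and type I error stayed below 5 % for the Wald tests in the scenarios tabulated. A reader might infer that the trial is underpowered or its primary test flawed; the figures do not support either.

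**What to change.** Before unblinding, state in the analysis plan that the primary logistic regression contains arm, EuroSCORE stratum, age (continuous) and baseline MMSE (continuous). Give a simple rule for missing covariate values, for example replacement by the overall mean computed without regard to arm. Keep the EuroSCORE-only model as a named sensitivity analysis, and make sure age and MMSE are among the predictors in the imputation model.

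Report the standardised (marginal) risk ratio and risk difference from the adjusted model with 95 % confidence intervals, next to the odds ratio. These match the 50 % relative reduction used in the sample size and its recalculation.

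The cost is a few sentences, two extra coefficients (which about 55 expected events can support) and the missing-covariate rule. No new data collection is needed, and the sample size of 190 and the recalculation procedure can stay as they are, because neither relies on a covariate gain.

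### Neither stated test for secondary outcomes uses the baseline MMSE and Katz ADL scores already collected, an avoidable loss of efficiency whose size depends on a correlation the protocol does not give

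*Protocol article*

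**What the plan says.** The section Statistical analysis and sample size calculation gives one rule for continuous secondary outcomes, steered by the Shapiro-Wilk test. Data judged normal "will be compared using an analysis of covariance (ANCOVA) with the dichotomized EuroSCORE as binary covariate". For the rest, "Intergroup comparisons of non-normally distributed data will be performed using the stratified version of the" Mann–Whitney U test. The dichotomised EuroSCORE is the only covariate or stratifier on either route. The same section describes a direct-likelihood longitudinal model with unstructured covariance, but assigns it to laboratory markers.

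Secondary endpoints lists the "MMSE at postoperative day 3, day 5, the day before discharge and at 6 months post surgery", and Katz ADL at baseline, the day before discharge and 6 months. Baseline assessment places an MMSE on the day before surgery and adds that "preoperative functional status will be assessed using the Katz Index of Activities of Daily Living". Both baseline scores will therefore be on file.

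No SD, target difference or baseline correlation is given for either scale. The only sample size is for the primary endpoint.

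**The concern.** MMSE and Katz ADL are the only postoperative scales of cognition and daily function among the secondary endpoints, and the Discussion puts weight on long-term neurocognitive function. Part of the spread in a postoperative score is the spread that patients brought to surgery. A comparison that ignores the preoperative score leaves that part in the error term and does not correct a chance imbalance between arms.

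The normality switch adds to this. MMSE cannot exceed 30 and patients with dementia are excluded, so scores are likely to pile up near the top and fail Shapiro-Wilk. The analysis then moves to a rank test that uses no baseline and gives no adjusted effect size. At stake are wider intervals and lower power on these two outcomes.

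**Working it through.** **1. The plan's own figure.** Inputs from the sample size section: two-sided alpha of 5 %; "the incidence of POD after cardiac surgery with sevoflurane-anesthesia is approximately 40" %; the patients "are required to show with 80 % power a 50 % reduction in the incidence of POD", hence 40 % versus 20 %; continuity correction applied.

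- Uncorrected: n = [1.96·√(2·0.30·0.70) + 0.8416·√(0.40·0.60 + 0.20·0.80)]² / 0.20² = 81.2, so 82.
- Corrected: (81.2/4)·[1 + √(1 + 4/(81.2·0.20))]² = 90.95, so **91 per group**, as stated.
- The recalculation example (32 % versus 16 %) gives 123 per group in the same way, also as stated.

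None of this involves MMSE or Katz ADL, so the point below leaves it unchanged.

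**2. Effect of baseline adjustment.** Let r be the correlation between baseline and follow-up score within treatment group, beyond what EuroSCORE explains. Adjustment multiplies residual variance by (1 − r²). With 190 patients at 1:1, n = 95 per group:

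- Difference detectable at 80 % power without baseline: (1.96 + 0.8416)·√(2/95) = 0.406 SD.
- With baseline: 0.406·√(1 − r²).
- Power at 0.406 SD with baseline: Φ(2.8016/√(1 − r²) − 1.96).
- Equivalent unadjusted size: 95/(1 − r²) per group.

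r is an assumption, so a range is shown:

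| r | fall in variance | detectable difference (SD) | power at 0.406 SD | equivalent n per group |
|---|---|---|---|---|
| 0 | 0 % | 0.406 | 80.0 % | 95 |
| 0.2 | 4 % | 0.398 | 81.6 % | 99 |
| 0.3 | 9 % | 0.388 | 83.6 % | 104 |
| 0.5 | 25 % | 0.352 | 89.9 % | 127 |
| 0.7 | 49 % | 0.290 | 97.5 % | 186 |

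These are normal-theory figures with complete data.

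**3. Does the gain survive the rank route?** An illustrative simulation used scores rounded and capped at 30. The assumed mean and SD before capping were 28 and 2 at baseline, and 27 and 2.5 at follow-up. There were 95 per group, a shift of 0.41 SD, 1,500 runs per setting and no EuroSCORE strata. Shapiro-Wilk rejected normality in every run.

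| latent r | power, Mann–Whitney | power, rank ANCOVA with baseline |
|---|---|---|
| 0.3 | 78 % | 79 % |
| 0.5 | 78 % | 86 % |
| 0.7 | 75 % | 94 % |

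Type I error was 4 % to 6 % for both methods. The pattern matches step 2: little gain at r = 0.3, a clear one from about r = 0.5.

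**The case against.** **The gain may be small.** The document gives no r. Excluding dementia narrows the baseline spread, the ceiling weakens the correlation, and scores on day 3 or 5 may reflect acute illness more than prior cognition. At r = 0.2 to 0.3 the variance saved is only 4 % to 9 %. This stands: a reader might infer a large gain, but that needs r of about 0.5 or more, which nothing in the document establishes.

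**The rule is generic, and an analysis plan may refine it.** The article does not say that MMSE or Katz ADL enter as raw postoperative scores, or that each visit is analysed alone. The Katz endpoint is worded as functioning before and after surgery. So a change-score analysis is not ruled out, and visit-by-visit analysis of raw scores is an inference. Two things remain. The article states the covariate set rather than leaving it open, so a plan that added baseline would depart from it. And a change score would not close the gap: with equal variances at both times its variance is 2(1 − r) times that of the raw score, which is 1.4 at r = 0.3, 1.0 at r = 0.5 and 0.6 at r = 0.7, against 0.91, 0.75 and 0.51 with baseline adjustment.

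**The laboratory-marker model does not transfer directly.** It is specified for fixed times. The day before discharge is not fixed and may coincide with or precede day 5. Direct likelihood also assumes data missing at random, which is doubtful for patients untestable because of delirium, and it does not resolve deaths. This stands and shapes the fix.

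**Conclusion.** The point holds as one of efficiency on two secondary outcomes. Baseline MMSE and Katz ADL are collected, and neither stated route uses them. Over the assumed range r = 0.2 to 0.7, adjustment removes 4 % to 49 % of residual variance and lifts power at 0.406 SD, with 95 per group, from 80 % to between 81.6 % and 97.5 %. This rests on the assumed r and on complete data. That the rank route would apply is likely rather than certain.

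Two stronger readings are not supported. A reader might infer that the planned comparison is biased; randomisation keeps the unadjusted comparison valid, and simulated type I error was near 5 %. A reader might also infer that a null cognitive result would be uninformative; 0.406 SD is detectable at 80 % power without baseline, against 0.352 SD with it at r = 0.5. That is a loss, but not one that empties the result of meaning.

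**What to change.** - For MMSE and Katz ADL, pre-specify a baseline-adjusted comparison whatever the Shapiro-Wilk result: ANCOVA with the outcome's own baseline value and dichotomised EuroSCORE, using robust or bootstrap standard errors. Rank ANCOVA with baseline is an acceptable alternative.
- Keep the stratified Mann–Whitney test as a sensitivity analysis.
- If the longitudinal model is extended to MMSE, restrict it to the fixed times (day 3, day 5, 6 months) with a baseline-by-visit term, and analyse the pre-discharge score separately.
- Report deaths and untestable patients separately rather than relying on the likelihood model to absorb them.

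No new data are needed. The cost is a change of wording and minor analysis work, to be settled before unblinding so that the choice of covariate cannot look data-driven.
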